### Outcomes

2.5

The primary outcome of this study is spontaneous AVF maturation, which is defined as provision of sufficient blood flow for hemodialysis within 2 months of its creation without any interventional procedures. The secondary outcome is assisted AVF mature, which is defined as AVF maturation within 2 months from its creation, which is aided by any interventional procedure before successful use of AVF. The maturation time is defined as the period from the date of AVF creation to the date of the first successful employment for hemodialysis.

### Statistical plan

2.6

Continuous variables will be expressed as mean ± standard deviation, while nominal variables are expressed in frequency and percentage. Comparisons of continuous variables will be performed using the 2-tailed *t* test for unpaired samples or Welch *t* test as appropriate. Comparisons of nominal variables will be performed using the Chi-square test or Fisher exact test as appropriate. Multivariate logistic regression test will be used to evaluate the association between predictor variables and outcome variables. Statistical significance will be defined by a *P* value of <.05. The statistics will be performed using SAS 9.4 (SAS Institute Inc, Cary, NC).

G∗Power 3.1.9.4 was used to estimate the sample size to reach statistical significance in the *t* test. Assuming the effect size to be 0.6. Under the condition that α error is defined as 0.05; power was defined as 0.8; and the allocation ratio was defined as 1. Therefore, the sample size required to achieve statistical significance is 90 patients.

The data used for the study will be preserved and analyzed by the primary investigator. The data is accessible only to the primary investigator and study nurse for data safety. The data will be preserved for 2 years after the end of the study.

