## Introduction

1

In Taiwan, the burden of end-stage renal disease has been increasing tremendously over the last two decades. According to the 2017 Annual Report on Kidney Disease in Taiwan, the prevalence of patients requiring dialysis has increased from 1379 per million population in 2000 to 3317 per million population in 2015, thereby demonstrating an increasing rate of 11.1% per year.^[1]^ In patients on dialysis treatment, vascular access dysfunction is the most common cause of medical procedures, including angioplasty, thrombectomy, and placement of central venous catheters, thereby indicating a need for improved medical care associated with vascular access.^[2]^

Arteriovenous fistula (AVF) was introduced as a vascular access for hemodialysis by Brescia et al^[3]^ and remains the most commonly used vascular access to date.^[4]^ Due to its superior access patency and lower infection rates, AVF is the preferred vascular access for maintenance hemodialysis.^[5]^ However, AVF is not an ideal vascular access without drawbacks. One of its major flaws is that only 50% to 80% of the created AVFs achieve functional maturation for hemodialysis,^[6–8]^ which results in infectious and thromboembolic complications due to the prolonged use of the central venous catheter.

Previous studies have revealed several risk factors of AVF maturation failure, including anemia, advanced age, diabetes mellitus, and smoking.^[9,10]^ While these risk factors may be targeted to improve AVF maturation rate, modifiable risk factors for prevention are currently lacking.^[9]^ On the other hand, basic studies have revealed molecular pathogenic factors of AVF maturation failure, including localized inflammation, hypoxic injury, oscillating wall shear stress, uremic milieu, and oxidative stress.^[11]^ Despite these substantial studies exploring the role of pathogenic factors, modifiable pathogenic factors that are applicable for improvements in AVF maturation are lacking.^[12]^

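### The stated power of 0.8 with 90 patients rests on equal groups, but in this cohort the maturation rate sets the group sizes and no rate is given for the primary outcome

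*Protocol article*

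**What the plan says.** Section 2.6 (Statistical plan) sizes the study for a t test in G*Power. The inputs are an effect size ("Assuming the effect size to be 0.6"), a type I error ("α error is defined as 0.05"), and the statement that "power was defined as 0.8; and the allocation ratio was defined as 1". It concludes that "the sample size required to achieve statistical significance is 90 patients". The sample-size paragraph does not repeat the sidedness, but the comparisons of continuous variables in the same section are "performed using the 2-tailed".

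Section 2.2 describes a prospective observational study. Section 2.5 makes the primary outcome binary: spontaneous maturation within 2 months, with no interventional procedure. Aim 3 relates luminal pressure, a continuous measurement, to maturation. The only maturation rate in the document is in the Introduction: "only 50% to 80% of the created AVFs achieve functional maturation for hemodialysis".

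**The concern.** An allocation ratio is a design choice when investigators assign patients. Here they do not. Section 2.6 does not name the two groups of the t test, but pressure is continuous, maturation is binary, and no pressure cut-off is given that would form two pressure groups. The natural reading is that mean pressure is compared between fistulas that matured spontaneously and those that did not. The ratio is then the odds of maturation: 1 at a rate of 50%, about 2.3 at 70% and 4 at 80%.

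For a fixed total, equal groups give the highest power. A ratio of 1 is therefore the most favourable assumption available, and the protocol offers no rate for its primary outcome to support it. If the true rate is far from one half, the study has less power for its main aim than it reports, and a non-significant result would be weighed against a power that was not there.

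**Working it through.** **Inputs.** From section 2.6: d = 0.6, alpha = 0.05, power 0.8, ratio 1, N = 90, two-sided as for the comparisons in that section. The maturation rate p is treated as unknown. The Introduction's 50% to 80% is used as a guide only.

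**Formula.** Two-sample t test with n1 and n2 patients:
- degrees of freedom: n1 + n2 − 2 = 88
- critical value: t(0.975; 88) = 1.987
- noncentrality: d × √(n1·n2/(n1 + n2))
- power: probability that a noncentral t with this parameter lies beyond ±1.987

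**Step 1: reproduce the plan's figure.** With 45 + 45, the noncentrality is 0.6 × √(2025/90) = 0.6 × √22.5 = 2.846, and power is 0.804. With 44 + 44 (86 degrees of freedom), power is 0.795. So 90 is the smallest equal-group total that reaches 0.80. A one-sided test would need 72, so the stated figure is two-sided.

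**Step 2: keep N = 90 and let the maturation rate set the split.**

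| Rate (or its complement) | Split | n1·n2/90 | Noncentrality | Power | d detectable with 80% power |
|---|---|---|---|---|---|
| 50% | 45/45 | 22.5 | 2.846 | 0.804 | 0.60 |
| about 54% (46%) | 49/41 | 22.3 | 2.835 | 0.801 | 0.60 |
| 60% (40%) | 54/36 | 21.6 | 2.789 | 0.788 | 0.61 |
| about 62% (38%) | 56/34 | 21.2 | 2.760 | 0.779 | 0.62 |
| about 65% (35%) | 58/32 | 20.6 | 2.725 | 0.769 | 0.62 |
| 70% (30%) | 63/27 | 18.9 | 2.608 | 0.732 | 0.65 |
| about 75% (25%) | 68/22 | 16.6 | 2.446 | 0.677 | 0.69 |
| 80% (20%) | 72/18 | 14.4 | 2.277 | 0.615 | 0.75 |

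Power depends on the product n1·n2, so a rate and its complement give the same value. Splits are rounded to whole patients; at exactly 62% the power is 0.780.

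**Step 3: scale.** The chance of missing a true difference of d = 0.6 is 1 − 0.804 = 0.196 at a 50% rate, 1 − 0.732 = 0.268 at 70%, and 1 − 0.615 = 0.385 at 80%. To restore 0.80 power, the total would have to be 107 at 70% and 140 at 80%.

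**The case against.** The strongest reply is that the calculation contains no arithmetic error and states its ratio openly. That is true. A reader might infer that 90 is miscalculated; it is not, and the dispute is about one input.

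Second, the 50% to 80% range belongs to another endpoint. The Introduction reports functional maturation in earlier studies and mentions neither a 2-month limit nor a ban on interventions. Spontaneous maturation as defined in section 2.5 is narrower, so its rate may be lower and may lie near one half, where a ratio of 1 would be reasonable. This stands. It rules out the stronger reading that the study lacks its stated power over most of its own expected range, because the protocol states no expected range for its primary outcome. It does not rescue the ratio, though: a rate well below one half costs as much power as one equally far above it.

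Third, power is not very sensitive near one half. This also stands. Between about 38% and 62% the shortfall from 0.80 is about 2 points at most, which is of no practical importance.

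Fourth, the t-test groups are inferred. That is so, and the conclusion is conditional on the inference.

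A reader might also infer that 90 is too few because it leaves no margin for patients lost or not evaluable. The document gives no loss rate, and a condensed article may leave such an allowance to the full protocol, so that is not part of this point.

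**Conclusion.** The point holds as a stated power that the design does not secure. The 90 follows correctly from its inputs, but the ratio of 1 is an outcome of the study rather than a setting, and the document gives nothing to show that about half the fistulas will mature spontaneously. The consequence ranges from negligible (power about 0.78 or more for rates of roughly 38% to 62%) to material: 0.77 at 65%, 0.73 at 70% or 30%, 0.68 at 75%, and 0.61 at 80% or 20%. The effect detectable with 80% power rises from 0.60 to 0.75 between the middle and the extreme.

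This rests on three assumptions: the test is two-sided, the t-test groups are spontaneously matured versus not, and all 90 patients are analysed. It does not rest on applying the 50% to 80% range to the primary outcome. The statement should be corrected. The design, data collection and analysis are unaffected, so this ranks as something to fix rather than something that blocks the study.

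**What to change.** Keep 90 patients and replace the power statement in section 2.6 with wording such as:

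> With 90 analysed patients, power for d = 0.6 (two-sided alpha 0.05) is 80% if about half the fistulas mature spontaneously, 79% at 60% (or 40%), 73% at 70% (or 30%) and 61% at 80% (or 20%); the effect detectable with 80% power ranges from d = 0.60 to 0.75.

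Drop the statement that 90 is the number needed to reach statistical significance. A power of 0.8 means that a true effect of the assumed size would be missed in about one study in five, and no sample size guarantees significance.

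The cost is one sentence, and the reported figure becomes less favourable. No extra patients, visits or measurements are needed.

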### Ethics and dissemination

2.7

This study has been approved by the ethics committee and Institutional Review Board of Taipei Medical University (N201801091). All participants will sign the informed consent after being informed about the goals and methods of the study. The present study will be conducted in accordance with the tenets of the 1975 *Declaration of Helsinki*, as revised in 2000. The result of the study will be disseminated by publication as journal articles.

## Discussion

3

The contemporary theory for AVF maturation failure or loss of long-term AVF patency focuses on disturbed wall shear stress. With the creation of AVF, arterial blood flow is introduced into the venous system, raising the venous wall shear stress from 1–6 dyn/cm^2^ to 10–70 dyn/cm^2^, similar to the level in the arterial system. Because of the increased wall shear stress, the vein initiates outward remodeling, a process that expands vessel diameter and lowers wall shear stress towards its baseline level, forming the AVF for hemodialysis.^[19]^ For blood flow in a vessel, wall shear stress is estimated by the Haagen-Poisseuille equation as follows: 

where **μ** is the kinetic viscosity, **u** is the mean velocity, and **d** is the vessel diameter. Note that this equation can only be applied in vivo with the assumptions that blood is considered as a Newtonian fluid; the blood vessel is cylindrical, straight, and inelastic; and that blood flow is steady and laminar.^[20]^ The role of disturbed wall shear stress on AVF stenosis has been demonstrated in animal^[21]^ and computational^[22]^ models of AVF. Recently, shear stress has also been considered to be a potential key factor for AVF maturation.^[23]^ However, blood wall shear stress estimations requires complicated hemodynamic measurements and several assumptions that are difficult to be applied to human subjects, thereby making it hard to standardize wall shear stress in clinical studies.^[24]^ In the present study, we expect to demonstrate the association between AVF luminal pressure and AVF maturation, which may be modified pharmaceutically or surgically.
